## Number of participants to be included in the research

With a rate of lost to follow-up of < 2%, a population of 268 patients would guarantee a power of at least 80% to demonstrate at the 2-sided alpha risk of 5%, a difference of 10% to 14% between the 2 groups concerning the composite primary endpoint (4% vs 14% or 10% vs 24%). The number of patients to be recruited is fixed at 268.

## Considered degree of statistical significance

P<0.05

## Statistical research termination criterion

None.

## Management of missing, unused or invalid data

In this trial and considering that the protocol will be respected, no missing data are expected for the intervention, stratification and endpoint variables. Vital status at 28 days for patients discharged before D28 will be collected by telephone call by a member of the research team (as a precaution, the town of birth of each included patient will be noted at inclusion in order to collect vital status from city halls if necessary). Patients who withdraw their consent will be excluded from the analysis as required by French law, and it is not planned to replace them by imputation for the main analysis. However, the number of patients withdrawing their consent will be analyzed to assess whether it does not reveal an imbalance between the 2 randomization groups, which could be related to a less tolerance of either arm.

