## Secondary endpoints

The duration (in days) to improve the clinical WHO ordinal scale from randomization to 28 days between the 2 groups (PP and usual care). This scale is recommended by the WHO (<http://www.who.int/blueprint/priority-diseases/key-action/novel-coronavirus/en/>) and was used in clinical trial of COVID-19 (CAO; N Engl J Med; 2020). This scale is relevant but it could be difficult to use for overloaded wards during an epidemic to exhaustively survey all points. Moreover, because the unit of time is the day, the score is imprecise (e.g., for reasons of feasibility, it is not possible to envisage twice-daily surveying). For this reason, the scientific committee chose not to use this endpoint as primary endpoint.

The rate of endotracheal intubation (%) for invasive mechanical ventilation at 28 days between the 2 groups

The rate of non-invasive ventilation at two pressure levels at 28 days between the 2 groups

The time passed on oxygen therapy from inclusion to day 28 between the 2 groups

The hospital length of stay between the 2 groups

The mortality at 28 days and during the hospital stay between the 2 groups

The rate of transfer to ICU at 28 days

The rate of use of non-invasive ventilation at 2 levels pressure and intubation over the entire hospital stay.

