## Research duration

Inclusion period: Epidemic COVID-19 period

Duration of intervention: the study intervention will stop when one of the events is reached: initiation of non-invasive or invasive ventilation, death, or patient still hospitalized at day 28 without event. Patients hospitalized for > 28 days will continue to be followed in the study (rate of use of resuscitation, rate of use of non-invasive or invasive ventilation, death).

The duration of participation for each patient corresponds to the hospitalization duration (all wards combined), subject to AEs that would require a longer follow-up.

Total duration of participation in the study for the patient: length of hospitalization

Total duration of the study: 24 months

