## Statistical methods

A detailed analysis plan will be developed prior to the start of the study. The plan will be modified, if necessary, before the statistician is unblinded.

Oatient characteristics will be described by randomization group as number and percentages for categorical variables and mean (standard deviation) or median (25th and 75th percentile) for continuous variables, depending on their distribution.

The main analysis will be conducted on an intention-to-treat basis. However, data for patients withdrawing their consent during the study, in accordance with French law, will not be analyzed.

The primary endpoint (percentage of patients requiring intubation or non-invasive ventilation at 2 pressure levels, or who died within 28 days of inclusion) will be compared between the 2 groups (PP and usual care) by a Mantel-Haenszel 2-test stratified on the stratification variables #2 and #3 (SpO2 and BMI). The effect of the intervention will be expressed in terms of absolute risk difference and its 95% confidence interval (CI). The result of this analysis will be confirmed by a mixed-effect logistic regression analysis, with the recruiting center as the random effect and the study intervention and the stratification variables 2 and 3 as fixed effect variables. Interaction terms between the stratification variables and the intervention will be introduced into the model and retained only if they show a significant effect on the frequency of the outcome. Logistic regression analysis will be used to estimate the odds ratio and its 95% CI.

The binary secondary endpoints (intubation rate, rate of non-invasive ventilation at 2 pressure levels, rate of transfer to ICU, mortality) will be compared between the groups using the same method.

The time to clinical improvement (decrease of 2 points on the WHO scale) will be compared between groups by log rank test and presented as Kaplan-Meier curves. The difference in risk between the groups will be expressed as a hazard ratio (HR) and its 95% CI. This analysis will be secondarily adjusted for stratification variables, and possibly other covariables that would be misbalanced between groups, using a Cox proportional model provided the proportional assumption is verified.

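### The primary endpoint runs to day 28, but after discharge the protocol provides only for collecting vital status, so the two ventilation components are not secured to day 28

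*Protocol*

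**What the plan says.** Section 8.1 defines the primary outcome as the "percentage of patients requiring intubation or non-invasive ventilation at 2 pressure levels, or who died within 28 days of inclusion". The secondary endpoints use the same horizon for the rates of intubation, two-level non-invasive ventilation and ICU transfer, and for oxygen: "The time passed on oxygen therapy from inclusion to day 28 between the 2 groups".

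Follow-up is described differently. Section 5.4 states: "Total duration of participation in the study for the patient: length of hospitalization". The synopsis agrees, and both extend participation only for adverse events that need it. Patients still in hospital after day 28 stay under observation. The last column of the schedule in section 5.3 is hospital discharge or ICU with mechanical ventilation, and the table has no day-28 contact.

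For patients who leave before day 28, section 8.5 says: "Vital status at 28 days for patients discharged before D28 will be collected by telephone call by a member of the research team". Town halls are the back-up source. Section 5.6 takes all data not on its CRF list from the hospital record. Section 8.5 also expects no missing values for the endpoint variables, provided the protocol is respected. Section 11.4 nevertheless refers to a follow-up of 28 days.

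**The concern.** Of the three components of the composite, only death has a stated route of collection between discharge and day 28. A telephone call about vital status, or a town hall register, does not show whether a survivor was intubated or received two-level ventilation.

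These components carry most of the endpoint. The primary objective section argues that, because patients with a do-not-intubate order are excluded, only a sudden death unlikely to be respiratory would enter the composite without prior ventilation. The components expected to supply nearly all the events are therefore the ones without assured follow-up.

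Two further features matter. A shorter stay is a stated secondary objective, and blinding is not feasible. Time to discharge, and with it the unobserved time before day 28, could differ between arms. The 28-day rates of intubation, non-invasive ventilation and ICU transfer share the gap, as does oxygen time for a patient sent home on oxygen.

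**Working it through.** **Inputs.** From section 8.2: "a power of at least 80% to demonstrate at the 2-sided alpha risk of 5" (per cent); rates of "4% vs 14% or 10% vs 24" (per cent); loss to follow-up below 2%; and "The number of patients to be recruited is fixed at 268". Allocation is 1:1 (synopsis), so there are 134 per arm, and 134 × 0.98 ≈ 131 after loss. The share of failures that are non-fatal and occur unseen after discharge is not given anywhere. Every value used for it below is an assumption.

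**Step 1: reproduce the plan's figure.** Pooled normal test without continuity correction, with p̄ the mean of the two rates:

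n per arm = [1.96·√(2p̄(1−p̄)) + 0.8416·√(pC(1−pC) + pP(1−pP))]² / (pC − pP)²

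- 4% vs 14%: n = 127.4, so 128 per arm, 256 in total, and 256/0.98 = 262 after loss.
- 10% vs 24%: n = 111.8, so 112 per arm, 224 in total, and 224/0.98 = 229 after loss.

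The planned 268 covers both. Power = Φ[(Δ − 1.96·SE0)/SE1], where SE0 is the pooled and SE1 the unpooled standard error. With 131 per arm:

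- 4% vs 14%: (0.10 − 1.96 × 0.03536)/0.03482 = 0.882, power 81.1%.
- 10% vs 24%: (0.14 − 1.96 × 0.04641)/0.04560 = 1.075, power 85.9%.

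The sample-size arithmetic stands. The question is what is observed.

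**Step 2: the same proportion missed in both arms.** If k control-arm points are missed, the missed share is m = k/pC and both observed rates are multiplied by (1 − m). Example: k = 1 at 14% gives m = 7.1%, observed rates 13.0% and 3.71%, and a difference of 9.29 points.

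| Control points missed | Share of failures at 14% | Power, 4% vs 14% | Share of failures at 24% | Power, 10% vs 24% |
|---|---|---|---|---|
| 0 | 0 | 81.1% | 0 | 85.9% |
| 0.5 | 3.6% | 79.5% | 2.1% | 85.0% |
| 1 | 7.1% | 77.8% | 4.2% | 84.1% |
| 2 | 14.3% | 74.2% | 8.3% | 82.1% |
| 3 | 21.4% | 70.1% | 12.5% | 79.9% |

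At 0.25 points the first scenario still has 80.3%. It has little margin, whereas the second stays at or very near 80% throughout.

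**Step 3: unequal loss with no true effect.** Take 14% in both arms, with the prone arm under-counted by d points more than control. The probability of a significant result favouring prone positioning is Φ[(d − 1.96·SE0)/SE1], with rates 0.14 and 0.14 − d:

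| Extra under-count, prone arm | Share of its failures | False-benefit probability |
|---|---|---|
| 0 | 0 | 2.5% |
| 0.5 points | 3.6% | 3.3% |
| 1 point | 7.1% | 4.2% |
| 2 points | 14.3% | 7.0% |
| 3 points | 21.4% | 11.0% |

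If the extra under-count fell in the control arm, the error would go the other way.

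**The case against.** A reader might infer that the protocol scores post-discharge ventilation as no failure and that the call asks about nothing but survival. It says neither. No scoring rule is given, section 8.5 does not use the word only, and neither the call script nor a full CRF is shown. The statistical analysis plan, which is also not shown, could set the scoring.

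The gap is also narrower than it first looks. A patient ventilated after discharge who dies by day 28 still counts, through death. Section 5.6 does not limit the hospital record to the index stay, so a readmission to the same hospital could be found. Adverse-event follow-up may catch some cases, although section 7.2 narrows reporting. Section 11.4 implies that 28 days of follow-up were intended. Light follow-up also suits a pragmatic trial in overloaded wards.

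The illustrative losses may be too large. Missing 1 to 3 points of 14 means that 7% to 21% of control failures are non-fatal, occur after discharge and go undetected, and nothing in the documents supports such shares. The false-benefit figures for 2 and 3 points also require an intervention that does not change failure yet shifts discharge enough to hide those events.

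These arguments limit the size and certainty of the concern but do not remove it. The reference in section 11.4 conflicts with section 5.4 and does not supply the missing data collection. An analysis plan can set a scoring rule, but it cannot recover information that nobody asked for.

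**Conclusion.** The concern holds as an inconsistency between the endpoint window and planned data collection. The protocol defines a 28-day composite, ends participation and scheduled assessment at discharge, and names only vital status for collection afterwards. Its expectation of complete endpoint data is therefore not secured for intubation and two-level ventilation. The patients at risk of misclassification are those discharged before day 28, ventilated later (most plausibly elsewhere) and alive at day 28. Counting them as event-free is the probable result, not a stated rule.

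Size and direction are uncertain. It is tempting to conclude that the gap favours prone positioning because that arm may go home sooner. The documents do not support this: shorter stay is a hypothesis, events would have to fall in the extra days at home, and equal proportional loss shrinks the difference and so works against the intervention. Nor do they show that the 80% power target is missed. That depends on the assumed loss, and under 10% vs 24% power is still 79.9% with three control points missed.

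This should be fixed before the endpoint data are collected. It is not an error in the sample size.

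**What to change.** - In the day-28 call already planned, also ask about readmission, intubation, two-level non-invasive ventilation, ICU stay and the date oxygen was stopped. Confirm positive answers from hospital records where they can be obtained.
- Add the day-28 contact to the schedule table in section 5.3.
- State in the synopsis and in sections 5.4 and 8.5 that follow-up for the primary endpoint runs to day 28 for all patients, and bring this into line with sections 8.1 and 11.4.
- State how unknown ventilation status after discharge is scored, with a sensitivity analysis.

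The cost is a few more questions in the call, one CRF page, some recall error and some requests for outside records. The budget in section 13.1 does not list the call, so its resourcing should be checked.

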## Selection of participants to be included in the analysis

The main analysis will be conducted on an intention-to-treat basis. However, data for patients withdrawing their consent during the study, in accordance with French law, will not be analyzed.

A per-protocol analysis including only patients who performed at least 2 hr of PP during the day in the PP group and patients in the usual care group who did not perform PP, is planned.

# Data and source document access rights

## Data access rights

In accordance with Good Clinical Practice (GCP):

- The sponsor is in charge of obtaining the approval of all parties involved so that direct access is ensured to the sites where the trial takes place, to the source data, to the source documents and to the reports. The purpose of this being that the sponsor will be able to carry out quality control and audit.

- Investigators shall provide the persons in charge of follow-up, quality control or audits with the research documents and individual data strictly necessary for those purposes, according to the provisions of French Law (articles L.1121-3 and R.5121-13 of the French Public Health Code).

## Source documents

Source documents are defined as any documents or original objects that could be used to prove the existence or accuracy of data or any events occurring during the study. They will be kept for 25 years by the investigator or the hospital if it is a medical hospital record.

All the information requested for the protocol will be recorded in the CRF in paper format.

## Data confidentiality

In accordance with the provisions concerning the confidentiality of the data made available to the persons in charge of quality control of biomedical research (article L.1121-3 of the French Public Health Code), in accordance with the provisions concerning the confidentiality of the information on the nature of the products, trials, the consenting parties and the results (article R. 5121-13 of the French Public Health Code), persons with direct access shall take the necessary precautions to ensure the confidentiality of the information of the products, trials, the consenting parties, their identity and the results.

Those persons, and also the investigators themselves, are bound by professional secrecy ( articles 226-13 and 226-14 of the French penal code).

During the biomedical research or at its conclusion, the data collected on the consenting parties, sent by the investigators to the sponsor (or any other specialized operator) shall be anonymized.

Investigators should not, under any circumstances, reveal the name or contact details of the individuals concerned.

Only the first letter of the last name and the first letter of the first name of the patient will be registered, along with a coded number specific to the trial indicating the order of inclusion.

The sponsor shall ensure that each consenting party has given their written approval for access to their own individual data, strictly necessary for the research quality control.

# Quality control and assurance

A clinical research associate (CRA) assigned by the sponsor will ensure the proper conduct of the study, collection of written data, their documentation, recording and reporting, in accordance with the standard operating procedures implemented in the Orleans Regional Hospital, in accordance with GCP and with existing legislative provisions.

The investigator and their team members agree to make themselves available for the regular quality control visits carried out by the CRA. During these visits, the following elements will be revised:

- Written consent signed by the patient
- Adherence to the study protocol and the procedures defined
- Quality of the collection of the data in the CRF: accuracy, missing data, consistency with the source documents

Furthermore, the investigators undertake to agree to quality assurance audits conducted by the sponsor and to inspections carried out by the competent authority. All the data, documents and reports may be subject to audits and regulatory inspections without the possibility of opposing medical secrecy

# Ethical considerations

## Independent Ethics Committee

The trial protocol and information leaflet will be submitted to an independent ethics committee selected by drawing lots, for its opinion.

The notification of the favorable opinion from the independent ethics committee will be sent to the sponsor and to the competent authority.

For the Monaco center, the study documents will also be submitted to the Consultative Committee on Ethics in Biomedical Research (CCEMRB), which is the local authority of the Principality of Monaco. The study can only begin after their approval.

## Substantial amendments

In case of substantial modification to the protocol by the investigator, this modification will be approved by the sponsor. The sponsor will need to obtain a preliminary favorable opinion from the independent ethics committee before the substantial amendment can be made. A new consent will be collected from the participants if necessary.

## Patient information and consent form

Patients will receive comprehensive and accurate information about the study objectives, their right to refuse to participate in the trial or their possibility to withdraw from the study, in terms they are able to understand. All of this information will feature in the information leaflet given to the patient. The patients consenting to participation will have to date and sign the consent form. Refusal or consent will be specified by the investigator in the patient’s medical record.

All of this information will feature in the information leaflet given to the patient. The written consent of the patient will be obtained by the investigator, in accordance with the Clinical trial involving human participants N°2 law, prior to final inclusion in the study.

The information letter and consent for patients in France are already validated by the CPP. The letter of information and consent for patients in the Principality of Monaco will be examined by the CCEMRB (compliance with the Monegasque law).

A consent form will be completed by the investigator and by the patient in order to trace the agreement of the patient's consent. A copy of the information and consent form will be given to the patient, the investigator will keep the original.

## Definition of the exclusion period

Patients included in the study will be allowed to participate in another study EXCEPT a study assessing prone position in the COVID-19 in medical wards (i.e., outside the ICU) during the 28-day follow-up. If the patient is transferred to an ICU, the study intervention will stop and the ICU practitioners will be free to care for the patient as they wish. During the SARS-CoV-2 epidemic, in the absence of extensive knowledge about the best management modalities, clinical research evaluating the full range of drug and non-drug strategies is an international priority.

## Compensation

NA

## Registration of persons consenting to biomedical research on the national data file

NA

# Data and document use and storage

## Case report form (CRF)

An electronic CRF (eCRF) will be developed. However, a notebook will be provided with the data to be collected in real time.

All information required by the protocol must be recorded in the notebook and an explanation must be provided for each missing data. Data should be collected as they are obtained and transcribed into these notebooks in a neat and legible manner.

Erroneous data found on the CRFs should be clearly crossed out and the new data copied next to the crossed-out information, with initials, date, and possibly a justification by the investigator or authorized person who made the correction.

In the context of the COVID-19 epidemic, all paper documents will be placed in a plastic bag at the patient's discharge and kept for 5 days before opening it for analysis and data entry.

## Data input and data production

Data will be entered into an eCRF medsharing by the investigation team of each departments involved in the study.

## French data protection commission (CNIL-France)

This study is related to the "Reference Methodology" (MR-001) in application to Deliberation No. 2018-153 of May 3, 2018 approving a reference methodology for the processing of personal data implemented in the context of research in the health field with the collection of consent from the person concerned and repealing Deliberation No. 2016-262 of July 21, 2016.

Orleans Regional Hospital, the study sponsor, signed an undertaking to comply with this "Reference Methodology" on March 10, 2017.

Considering the automated data recording on Monegasque territory (eCRF), the file will be submitted to the Commission de Contrôle des Informations Nominatives (CCIN) of Monaco for advice.

## Archiving

The following documents will be archived under the study title in the Research Department of Orleans Regional Hospital until the end of the period of use.
The documents include:
→ Protocol, appendices and potential amendments
→ Information leaflet
→ Individual data (authenticated copies of raw data)
→ Follow-up documents
→ Statistical analysis
→ Final study report
At the end of the practical use period, all archiving documents will be placed under the responsibility of the sponsor for 25 years after the end of the study, in accordance with institutional practices.

Documents shall not be moved or destroyed without the sponsor’s agreement. At the end of the 25-year period, the sponsor shall be contacted concerning destruction. All data, documents and reports will be subject to audit or inspection.

